**Methods/Design:**

We aim to investigate the hypothesis that prophylactic use of a cervical pessary will be effective in the prevention of preterm delivery and the neonatal mortality and morbidity resulting from preterm delivery in multiple pregnancy. We will evaluate the costs and effects of this intervention. At study entry, cervical length will be measured. Eligible women will be randomly allocated to receive either a cervical pessary or no intervention. The cervical pessary will be placed in situ at 16 to 20 weeks, and will stay in situ up to 36 weeks gestation or until delivery, whatever comes first.

The primary outcome is composite bad neonatal condition (perinatal death or severe morbidity). Secondary outcome measures are time to delivery, preterm birth rate before 32 and 37 weeks, days of admission in neonatal intensive care unit, maternal morbidity, maternal admission days for preterm labour and costs. We need to include 660 women to indicate a reduction in bad neonatal outcome from 7.2% without to 3.9% with a cervical pessary, using a two-sided test with an alpha of 0.05 and a power of 0.80.

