### Participants

All women presenting with a multiple pregnancy between 12 and 19 weeks of gestation are eligible for the study. We propose to also include women with monochorionic pregnancies as well as women with a triplet pregnancy or women with a previous preterm birth. Women with multiple pregnancies in which at least one of the foetuses has major congenital anomalies known at study entry will not be included. Gestational age will be determined from the menstrual history and confirmed from the measurement of foetal crown-rump length (of the bigger twin) at a first-trimester scan.

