### Procedures, recruitment, randomisation and collection of baseline data

All eligible women who present at one of the participating clinics will be referred to an obstetrician or a specifically appointed research nurse/midwife for counselling. They will receive an information sheet and, where possible, are given two weeks time to reflect on participation.

Once a patient has given informed consent, and the patient data have been entered in a web-based database, randomisation will be done over the internet.

Randomisation will be stratified for centre, parity (previous vaginal delivery or not), chorionicity (multichorial versus monochorial) and number of multiples (twin or higher order gestation).

We will apply block randomisation with a variable block size and a minimalisation procedure. The pessaries will be packaged according to the randomisation sequence at the central consortium office in Amsterdam, the Netherlands. Randomisation will be 1:1 for cervical pessary versus no treatment.

The study will not be blinded.

Baseline demographic, past obstetric and medical histories will be recorded for all women. Cervical length will be measured by transvaginal ultrasound at the time of randomisation or at the next visit.

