### Intervention

Eligible women will be randomly allocated to receive either a cervical pessary (Arabin pessary) or no intervention. The cervical pessary will be placed in situ at 16 to 20 weeks, and will stay in situ up to 36 weeks gestation or until delivery, whatever comes first.

All women participating will have a transvaginal measurement for cervical length between a gestational age of 18 to 22 weeks. Next to this research intervention cases are treated according to the local protocol in the participating clinics and other interventions i.e. tocolysis and corticosteroids in case of a threatened preterm birth can be carried out as usual. Furthermore no extra interventions will be needed. The use of progesterone is allowed, but this will mainly depend on the outcome of our current AMPHIA study[10].

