### Data analysis

Data will initially be analysed according the intention to treat method. The main outcome variable, 'bad neonatal outcome', will be assessed by calculating rates in the two groups, relative risks and 95% confidence intervals as well as numbers needed to treat. To evaluate the potential of each of the strategies, we will also perform a par protocol analysis, taking into account only those cases that were treated according to protocol.

Time to delivery will be evaluated by Kaplan-Meier estimates, with account for differing durations of gestation at entry, and will be tested with the logrank test. The other secondary outcome measures will be approached similarly to the primary outcome measure.

We plan a separate analysis of women with a cervical length below 25 mm at 18 tot 22 weeks, and we will look at interaction between cervical length and treatment effect.

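### The short-cervix subgroup and the length-by-treatment analysis rest on a cervical length at 18-22 weeks that need not precede, and for many women must follow, pessary placement

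*Protocol article*

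**What the plan says.** All places are in the protocol article.

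- **Data analysis:** "We plan a separate analysis of women with a cervical length below 25 mm at 18 tot 22 weeks". The same sentence continues that "we will look at interaction between cervical length and treatment effect".
- **Intervention, device:** "The cervical pessary will be placed in situ at 16 to 20 weeks". Controls receive no device.
- **Intervention, scan:** "All women participating will have a transvaginal measurement for cervical length between a gestational age of 18 to 22 weeks".
- **Abstract, Methods/Design:** "At study entry, cervical length will be measured".
- **Procedures, recruitment, randomisation and collection of baseline data:** "Cervical length will be measured by transvaginal ultrasound at the time of randomisation or at the next visit". The same section states that "The study will not be blinded".
- **Participants:** "All women presenting with a multiple pregnancy between 12 and 19 weeks of gestation are eligible for the study".

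The article therefore times the scan in three ways: at entry, at randomisation or the visit after it, and at 18-22 weeks. The Data analysis section names the last. No section says that the scan precedes insertion.

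**The concern.** A subgroup comparison keeps the protection of randomisation only if treatment cannot affect who enters the subgroup. Here the treatment is a device fitted at the cervix and the subgrouping variable is the length of that cervix, read in a window that opens two weeks after the placement window opens. The device could change the true length, or change the reading while it is in place. The sonographer can know the allocation, because the trial is open.

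In either case the women below 25 mm in the pessary arm would not be the counterparts of the women below 25 mm among controls. The subgroup result could then show benefit or harm where there is none, or mask a real effect. It is the only subgroup analysis the article names, and the Discussion looks ahead to pooling with other pessary trials, so a distorted result could be carried further.

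**Working it through.** The article gives no sample size, power or expected result for this analysis, so there is no figure of its own to reproduce. The check has three steps.

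**1. The windows (from the Intervention section)**

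Placement is at 16-20 weeks and the scan at 18-22 weeks.

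- Placement before 18 weeks: the scan must follow.
- Scan after 20 weeks: placement has already happened.
- Only when both fall between 18 and 20 weeks can the scan come first.

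Illustration, assuming the two timings are independent and uniform over their windows: P(both in 18-20) = 1/2 × 1/2 = 1/4. Within that square the scan is first half the time, so P(scan first) = 1/4 × 1/2 = 1/8. P(scan after placement) = 1 − 1/8 = 87.5%.

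The earlier scan described in the Abstract and the Procedures section cannot be the 18-22-week scan for a woman who enters and is scanned well before 18 weeks. The article does not say whether there are two scans, and the option of the next visit does not guarantee a reading before placement.

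**2. The subgroup when the pessary has no effect on outcome**

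Assumed inputs, none of them in the article: length L normal with mean 38 mm and SD 9 mm; log-odds of bad neonatal outcome falling 0.08 per mm; the device shifts the reading by s mm in the pessary arm only. The overall risk is set to the 7.2% in the Sample size section.

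Share below 25 mm: Φ((25 − s − 38)/9) in the pessary arm, with s = 0 in controls.

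- Controls: Φ(−1.444) = 7.4%
- s = −3: Φ(−1.111) = 13.3%
- s = +3: Φ(−1.778) = 3.8%

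Subgroup RR = E[p(L) | L < 25 − s] / E[p(L) | L < 25]. The RR at 25 mm or more is formed in the same way.

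| Shift s (mm) | Pessary arm below 25 mm | Risk below 25 mm, pessary v control | RR below 25 mm | RR at 25 mm or more |
|---|---|---|---|---|
| −3 | 13.3% | 17.1% v 20.0% | 0.86 | 0.92 |
| −1 | 9.1% | 19.0% v 20.0% | 0.95 | 0.97 |
| 0 | 7.4% | 20.0% v 20.0% | 1.00 | 1.00 |
| +1 | 6.0% | 21.1% v 20.0% | 1.05 | 1.02 |
| +3 | 3.8% | 23.4% v 20.0% | 1.17 | 1.06 |

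A second set of assumptions (mean 36 mm, SD 8 mm, measurement SD 3 mm, log-odds −0.06 per mm) gives, by simulation, a subgroup RR of about 0.86, 0.92, 1.08 and 1.14 for shifts of −4, −2, +2 and +4 mm, and 0.99 (1 within simulation error) for no shift.

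**3. The interaction**

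Let A = 1 for pessary, let M be the reading, and let logit p = α + βL with no treatment effect.

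- *Constant shift.* M = L + sA, so logit p = α + βM − βsA. The shift moves the treatment term by −βs and adds no M × A term. An interaction with continuous length is not biased.
- *Length-dependent shift.* M = L + A(s + kL). In the pessary arm L = (M − s)/(1 + k), so the slope on M is β/(1 + k) there and β in controls. The difference, β[1/(1 + k) − 1], is a false interaction, and it is zero only if k = 0.
- *Length cut at 25 mm, constant shift.* From the table, the ratio of the two stratum RRs is 0.86/0.92 = 0.93 for −3 mm and 1.17/1.06 = 1.10 for +3 mm. Both strata move in the same direction.

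**The case against.** **The order is not fixed.** The windows overlap at 18-20 weeks and entry runs to 19 weeks. For a late entrant, one scan can satisfy both the Procedures and the Intervention sections and still precede insertion. This stands. A reader might infer that every pessary-arm scan follows placement, but the documents do not show that. What they show is that the scan need not come first and in many cases cannot.

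**The interaction may be unharmed.** This stands for a constant shift and continuous length, as step 3 shows. A reader might infer that the interaction test is bound to be biased. That needs a shift that varies with length, on which the article is silent.

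**The inputs are invented and the artefact is small beside the noise.** Also true. Under the first set of assumptions, 330 women per arm give about 25 controls and 44 (shift −3) or 12 (shift +3) pessary women below 25 mm. With two children per woman and a design effect of 1 + (2 − 1) × 0.6 = 1.6, the RR of 0.86 has a 95% interval of about 0.34 to 2.14. The chance of a falsely significant result rises only from 5% to about 6%. The planned overall effect, 3.9/7.2 = 0.54, is far larger. This lowers the priority but does not justify the rule, because the bias would not shrink with pooling.

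**The background does not single these women out.** A reader might infer that it claims the strongest effect in short-cervix multiple pregnancies. It reports a strong effect in singleton pregnancies with a short cervix, and it describes the twin cohort without a cervical-length restriction.

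**Loss before the scan.** A reader might also expect deliveries before the scan to distort the subgroup. The article gives no rate for this: its earliest delivery band starts at 24 weeks, with 1.8% of women.

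**Conclusion.** The point holds for the subgroup rule as written. The 25 mm cut is applied to a reading that can be, and for many women must be, taken after a cervical device has been fitted in one arm of an open trial. The article also contradicts itself on when the scan takes place.

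The 87.5% rests on independent uniform timings. The relative risks of about 0.86 and 1.17 rest wholly on assumed inputs. The article does not say whether the pessary changes the reading, in which direction or by how much; with no change there is no bias. If there is a change, its size could not be separated afterwards from a real subgroup effect for women who have no reading before placement.

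A reader might infer that the trial's main result is at risk. It is not: the primary outcome, the sample size and the intention-to-treat comparison do not use this scan. The point should be fixed, but it is not critical.

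**What to change.** 1. Make the Abstract, Procedures, Intervention and Data analysis sections agree on how many cervical-length scans there are and when each is taken relative to randomisation and insertion.
2. Define the subgroup and the interaction by a length taken before randomisation or, at the latest, before pessary insertion, with the same gestational window in controls.
3. Fit that length as a continuous covariate in the interaction, and show the 25 mm cut as the displayed subgroup.
4. Report any later 18-22-week reading only as a descriptive post-randomisation measure.

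The cost is wording, plus fixing the timing of a scan that is already planned. The timing must be settled before data are collected, because a missing pre-placement reading cannot be recovered. The downside is that an earlier reading may predict preterm birth less well and put fewer women below 25 mm. Entry starts at 12 weeks, so a pre-randomisation scan could be up to 22 − 12 = 10 weeks earlier than the present window allows, and the 25 mm cut would then mean something different. The alternative of a reading before insertion, at matched gestation in controls, reduces that gap.

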### Interim analysis

An interim analysis will be performed after the inclusion of 300 women. This analysis will be done by an independent data and safety monitoring committee that will not be aware of the allocation of pessary or no treatment when they judge data on effectiveness. In case of severe side-effects, the safety monitoring committee can advise to stop the study.

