### Outcome measures

The main outcome parameter is the composite morbidity rate of children in the two groups. This composite morbidity rate contains the following variables: periventricular leukomalacia (PVL), severe Respiratory Distress Syndrome (RDS), Broncho Pulmonal Dysplasia (BPD), Intraventricular Haemorrhage II B or worse, Necrotizing Enterocolitis (NEC), proven sepsis and death before discharge from the nursery 24. They will be measured until 6 weeks after the expected term date of delivery.

Secondary outcome measures are time to delivery, preterm birth rate before 32 and 37 weeks, days of admission in neonatal intensive care unit, maternal morbidity, maternal admission days for preterm labour and costs. At present, a longer follow-up is not planned.

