### Statistical issues

#### Sample size

The sample size is calculated based on the primary outcome 'bad neonatal outcome'. In the control group, 'bad neonatal outcome' is expected in 7.2% of the children (1.8%*77% + 5.4%*35% + 7.2%*12% + 35.6%*8% + 50%*.5% = 7.2%). In this calculation, the first rate represents the probability that a patient delivers at that gestational age, whereas the second rate represents the probability of 'bad neonatal outcome' at that particular gestational age. In case of treatment, 'bad neonatal outcome' is then expected in 3.9% of the children (0.9%*77% + 2.7%*35% + 3.6%*12% + 17.8%*8% + 75%*.5% = 3.9%).

Because the outcomes in children from multiple pregnancies are to a certain extent non-independent, we adjusted our sample size assuming a correlation of 0.6 for composite neonatal morbidity between two children born from the same pregnancy[11]. Using a two-sided test with an alpha of 0.05 and a power of 0.80 we need 330 women in the control group and 330 in the intervention group (total of 660 women).

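### The interim committee judges the composite containing perinatal death without knowing the arms, and the plan states no route to learn which way an imbalance runs

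*Protocol article*

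**What the plan says.** All statements are in the protocol article.

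- **Interim analysis.** There is one look: "An interim analysis will be performed after the inclusion of 300 women". It is done by an independent data and safety monitoring committee, which "will not be aware of the allocation of pessary or no treatment when they judge data on effectiveness". The section then adds: "In case of severe side-effects, the safety monitoring committee can advise to stop the study". No other ground for stopping is given, and no unmasking step is described.
- **Abstract, Methods/Design.** "The primary outcome is composite bad neonatal condition (perinatal death or severe morbidity").
- **Outcome measures.** The list of components ends with "proven sepsis and death before discharge from the nursery". Time to delivery and preterm birth rates are secondary outcomes.
- **Procedures, recruitment, randomisation and collection of baseline data.** "The study will not be blinded", and "Randomisation will be 1:1 for cervical pessary versus no treatment".

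**The concern.** In many trials effectiveness and safety are measured by different events, so masking a committee for the first leaves the second intact. Here they overlap. If a device on the cervix did harm, for example by bringing births forward, the harm would be expected in the neonatal composite and in the secondary delivery outcomes. Those are effectiveness data, and the plan has the committee judge them without the allocation.

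Direction matters because the comparator is no treatment. A moderate imbalance in favour of the pessary is an ordinary reason to continue. The same imbalance against it, including deaths, may reasonably worry a committee much earlier. A committee that sees only the size of the difference cannot draw that distinction from those data. What is at stake is whether the one interim analysis described can serve as a safety check on the gravest outcome the trial records.

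**Working it through.** The plan gives no figure for this point, so there is none to reproduce. The check has two parts: reading the sections together, and a calculation of what the committee would see.

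**1. The sections side by side**

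- Effectiveness data are reviewed without the allocation (Interim analysis).
- The main effectiveness outcome contains death (Abstract; Outcome measures).
- So death, as a component of the composite, is reviewed without the allocation.
- The separate safety route covers severe side-effects. No masking is stated for it, but nothing says that perinatal death counts as a side-effect.
- No sentence provides for unmasking, and none forbids it.

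**2. What the look would show**

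Inputs:
- 300 women at the look out of 660 planned, or 300/660 = 45% of inclusions.
- 1:1 allocation, so 150 women per arm. Taking all as twins (an assumption, since triplets are allowed), that is 300 children per arm.
- Sample size section: "In the control group, 'bad neonatal outcome' is expected in 7.2% of the children". The pessary rate is 3.9% and the within-pregnancy correlation is 0.6.
- Assumptions: outcomes are complete for all 300 women, and masked means two coded groups, A and B.

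Steps:
- Expected affected children: 300 × 0.072 = 21.6 (control) and 300 × 0.039 = 11.7 (pessary).
- Design effect for pairs: 1 + 0.6 = 1.6.
- Pooled rate: (0.072 + 0.039)/2 = 0.0555.
- Standard error of the difference: √(0.0555 × 0.9445 × 2 × 1.6/300) = 0.02365.
- If the pessary works as planned: z = (0.072 − 0.039)/0.02365 = 1.40.
- If the same two rates are swapped, so the pessary is worse: z = (0.039 − 0.072)/0.02365 = −1.40.
- With coded arms the sign is unknown, so both cases show 21.6 against 11.7 and |z| = 1.40.
- Power at two-sided 0.05, with unpooled standard error √((0.072 × 0.928 + 0.039 × 0.961) × 1.6/300) = 0.02358: Φ((0.033 − 1.96 × 0.02365)/0.02358) = Φ(−0.57), or about 29%.
- Ignoring the correlation, z is about 1.77 and power about 42%.

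Even under the planned effect, then, the most likely picture is a moderate imbalance short of significance. A committee reads such a result mainly by its direction, and coded effectiveness data do not show the direction.

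**The case against.** Several counter-arguments have force.

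- **The masking is limited.** It is stated only for judging effectiveness. Side-effects have their own route with no masking stated, and unmasking is not prohibited. A reader might infer that the committee has no means at all of telling harm from benefit. The article does not support that: coded arms still reveal an imbalance, which could prompt a request to unmask. The control arm also receives no device, so device-specific side-effects can arise in one arm only. If the same codes run through all tables, they may give the allocation away. This stands, and limits the point to what the effectiveness data show by themselves.
- **A charter may cover it.** Unmasking rules are often set there, and a condensed article may omit them. This stands in part. The point does not rest on an omission, however: the article states a masking rule, and that rule reaches deaths.
- **Masking has a purpose.** A reader might infer from the open design that masking the committee is pointless or contradictory. It is neither. Clinicians who know each woman's allocation do not thereby know the accumulated comparison. Masking can also guard against prior belief about a device that, according to the Abstract and Discussion, some gynaecologists already use. The supportable statement is that masking protects little here, because the trial is open and the committee is independent.
- **The number of women affected.** A reader might infer that 330 − 150 = 180 further pessary allocations depend on the look. That would require complete outcomes at the 300th inclusion. Women enter at 12 to 19 weeks, and outcomes run to 6 weeks after the expected term date. Taking term as 40 weeks (an assumption), that is 46 − 19 = 27 to 46 − 12 = 34 weeks after entry. If recruitment continues meanwhile, fewer than 180 allocations remain to be influenced, and the article gives no basis for a specific number.

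**Conclusion.** The point holds in a limited form. Followed as written, the Interim analysis section has the committee review perinatal death and severe neonatal morbidity as effectiveness data without the allocation. From those data alone it can see the size of an imbalance but not whether it goes against the pessary. The one stopping ground named does not clearly include these events, and no route to unmasking is stated.

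The illustration (21.6 versus 11.7 affected children, |z| about 1.40, power about 29%) rests on twins only, complete outcomes for 300 women, the planning rates, a correlation of 0.6 and two coded groups. The conclusion about direction does not depend on those values.

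This is a weakness in the monitoring arrangement that should be corrected. It does not show that the committee would be unable to detect harm by any means, and it does not bear on the validity of the final analysis.

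**What to change.** Amend the Interim analysis section in two respects, and align the committee's charter with it:

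1. The committee sees perinatal death and the other components of the composite by allocated arm, or can be unmasked to them on request. By-arm results are kept from the investigators and the sponsor.
2. These events are stated to be part of the safety review, so that it is clear how they relate to the severe side-effects on which the committee may advise stopping.

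The cost is a change of wording, with no extra patients or data. There are two small downsides. The committee's judgement of effectiveness is less shielded from prior belief about the device, and it must keep by-arm results confidential. Unmasking on request, rather than routinely, would preserve more of the present arrangement and still meet the concern.
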